### Pupillometry Reliably Measures LC-NE Functioning in Clinical Settings

LC-NE activity causes a dilation of the eye’s pupil. This pathway is indirect, as the LC-NE inhibits the Edinger-Westphal nucleus that typically emphasizes pupil constriction [30]. Pupil dilation has historically been used as an indicator of arousal and cognitive load [31]. Recently, pupil dilation has been differentiated into a baseline pupil size (BPS) and a stimulus-evoked pupillary response (SEPR), which index changes in LC-NE tonic and phasic activity, respectively [32]. These indices are assessed by pupillometry in video-based eye tracking. A study of combined functional magnetic resonance imaging and pupillometry showed a correlation of the LC’s signal with pupil dilation during the resting state (BPS) and with pupil dilation to oddball stimuli (SEPR) [33]. In a nonhuman primate model, an LC-NE stimulation predicted pupil dilation after 200‐300 milliseconds [34]. Other subcortical regions elicited pupil dilation with larger delays, which indicated an indirect activation of the LC [35]. In an optogenetic mouse model, pupil dilation marked relative changes in LC-NE activity, whereas variability challenges pupil size as a readout of absolute LC-NE activity [36]. This can be addressed by the application of baseline-corrected metrics [37]. In humans, the assessment of LC-NE activity is difficult with magnetic resonance imaging and electroencephalography (EEG) due to the LC’s location and small size [38]. This is pronounced in children that often induce more movement artifacts. Pupillometry now provides an index of LC-NE tonic and phasic activity (BPS and SEPR) that can be reliably measured with eye tracking. This innovative neuroimaging allows us to assess LC-NE functioning even in preschoolers in a clinical setting [5].

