### LC-NE Activity as a Neuro-Translator of Acute Stress Responses

Stress like adverse childhood experiences is the other important determinant of psychopathology. An acute stress response is an internal coping mechanism to stress triggered by a neuronal network including the amygdala [57]. First, an autonomic response increases sympathetic activation for a momentary fight-flight-or-freeze response. A hypothalamic-pituitary-adrenal (HPA) axis then releases glucocorticoids like cortisol for sustained physical readiness. This endocrine stress response initially supports stress coping but cumulatively upregulates the HPA axis, which ultimately wears the body [58]. It explains the negative impact of stress over time. However, the acute stress response is also translated to a neuronal excitability that shapes our immediate perception in the face of stress [59].

This immediate neuro-translation of stress is moderated by LC-NE functioning [60]. The LC-NE has been established to initiate the autonomic stress response [61]. In addition, the HPA axis expresses a corticotropin-releasing hormone that binds to LC receptors and upregulates LC-NE tonic activity early in the endocrine stress response [62]. The upregulation of LC-NE tonic activity attenuates LC-NE phasic activity, which increases stimulus reactivity at the expense of sensory selectivity [63]. It reflects hyper-arousal [64] that intensifies the impact of stress [13]. For example, a liability to social stress in rodents was explained by an LC-NE modulation [65]. In humans, anxiety and stress-related disorders have been associated with increased LC-NE tonic activity [53,66]. Excessive LC-NE tonic activity in response to stress-inducing adversity might be an etiological mechanism of anxiety symptoms [62,66] that warrants an empirical evaluation in longitudinal studies.

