### Neurophysiological Measures

BPS and SEPR are assessed for each trial in each task. BPS is defined as the pupil size prior to stimulus onset, while SEPR represents a pupil size change in response to stimuli. BPS and SEPR will be evaluated in the auditory oddball task in response to standard trials as neurophysiological habituation [99] and to oddball trials as sensory selectivity [33].

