#### Statistical Analysis Plan

Structural equation models will be applied to estimate the associations between the latent constructs (LC-NE functioning, transdiagnostic psychopathology, and childhood adversity). A best-fit path model will be used to reduce the complexity of the structural equation in the longitudinal study of Objective 3. A latent mediation model, in which LC-NE functioning is expected to mediate an association between previous childhood adversity and transdiagnostic psychopathology, will be applied. Independent models for BPS, SEPR, and each transdiagnostic factor will be estimated. Classification approaches will be applied in exploratory analyses to identify LC-NE function profiles in subgroups of psychopathology.

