#### Expected Outcome and Study Hypotheses

We hypothesize associations between retrospective childhood adversity, LC-NE function, and transdiagnostic psychopathology. For example, lower LC-NE tonic activity is expected to represent a resilience to the negative impact of childhood adversity on psychopathology. In addition, we expect profiles of LC-NE functioning that are associated with patterns of transdiagnostic psychopathology; BPS is expected to positively correlate with the p-factor, whereas increased and decreased SEPR are expected to positively correlate with internalizing and externalizing symptoms, respectively.

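### Task 2.2 fits BPS and SEPR in separate models; if the two indices are correlated across children, the SEPR-only path also carries part of any BPS effect

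*Protocol article*

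**What the plan says.** The Task 2.2 statistical plan sets out a latent mediation model, with LC-NE functioning between childhood adversity and psychopathology, and then states: "Independent models for BPS, SEPR, and each transdiagnostic factor will be estimated". That is two indices by three factors (internalizing, externalizing, p-factor).

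The Neurophysiological Measures section of Work Package 1 has both indices taken on each trial: "BPS is defined as the pupil size prior to stimulus onset, while SEPR represents a pupil size change in response to stimuli". The introductory section on pupillometry says of variability in absolute pupil size: "This can be addressed by the application of baseline-corrected metrics".

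The introductory section on acute stress responses states: "The upregulation of LC-NE tonic activity attenuates LC-NE phasic activity, which increases stimulus reactivity at the expense of sensory selectivity".

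The Task 2.2 hypotheses give the indices different roles. For tonic activity: "BPS is expected to positively correlate with the p-factor". For phasic activity: "increased and decreased SEPR are expected to positively correlate with internalizing and externalizing symptoms, respectively".

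No listed covariate is the other pupil index. Task 2.1 names age, gender and IQ. Task 3.1 names adversity, earlier psychopathology and clinical support.

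**The concern.** The hypotheses separate a tonic route to general psychopathology from a phasic route whose sign distinguishes internalizing from externalizing. To support that separation, each effect must be estimated net of the other. A model with SEPR alone does not do this if BPS and SEPR are correlated across children and BPS is related to the outcome.

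The protocol's own theory makes a correlation plausible. Stress raises tonic activity, which lowers phasic activity, and stress in the form of adversity is the exposure in the Task 2.2 mediation model. A low-SEPR association with externalizing could then partly be a BPS association. A high-SEPR association with internalizing could be understated. With a positive correlation, both errors would run the other way.

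**Working it through.** **Inputs from the protocol.** Task 2.2 has 300 children, a path of 0.2 between LC-NE functioning and psychopathology (taken here as standardized) and stated power of .80.

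**Assumptions.** Two-sided 5% test. The BPS effect is 0.2, borrowed from the protocol's path for LC-NE functioning, which is not specific to BPS. The correlation rho is not given and is shown as a range.

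**The plan's own figure.** With Fisher z, power = Φ(√(n−3)·atanh|r| − 1.96) + Φ(−√(n−3)·atanh|r| − 1.96). For r = 0.2 and n = 300: √297 = 17.23, atanh(0.2) = 0.2027, product 3.494, power 0.937. If each construct has reliability 0.80, the observed r is 0.2 × 0.80 = 0.16 and power is 0.794. The stated .80 is therefore plausible. It cannot be reproduced exactly, because the simulation settings are not given, and it is not disputed here.

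**Identity.** With standardized variables, the SEPR-only coefficient is b_SEPR + rho × b_BPS. In the mediation model the same holds for the mediator-to-outcome path, with rho replaced by the coefficient of BPS on SEPR given adversity.

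**Case A: BPS effect 0.2, SEPR effect 0.** The joint model includes both indices (simulation, 4,000 runs).

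| rho | SEPR-only coefficient | False-positive rate, SEPR-only | False-positive rate, joint |
|---|---|---|---|
| -0.1 | 0.2 × -0.1 = -0.02 | 0.064 | 0.046 |
| -0.3 | 0.2 × -0.3 = -0.06 | 0.179 | 0.045 |
| -0.5 | 0.2 × -0.5 = -0.10 | 0.409 | 0.048 |
| +0.3 | 0.2 × 0.3 = +0.06 | 0.187 | 0.049 |

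The SEPR-only rates at negative rho are from Fisher z; simulation gave 0.065, 0.180 and 0.402. The rate at +0.3 is simulated; Fisher z gives 0.179.

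**Case B: SEPR effect 0.2 and BPS effect 0.2, both on internalizing.**

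| rho | SEPR-only coefficient | Power, SEPR-only | Joint estimate | Power, joint |
|---|---|---|---|---|
| -0.1 | 0.18 | 0.88 | 0.20 | 0.945 |
| -0.3 | 0.14 | 0.68 | 0.20 | 0.907 |
| -0.5 | 0.10 | 0.41 | 0.20 | 0.856 |
| +0.3 | 0.26 | 0.996 | 0.20 | 0.930 |

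**Case C: SEPR effect 0.2, no BPS effect on internalizing.** The SEPR-only estimate stays at 0.20 with power of about 0.94 at every rho. There is no attenuation.

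**Case D: SEPR effect -0.2 and BPS effect 0.2 on externalizing, rho -0.3.** SEPR-only gives -0.2 + (-0.3 × 0.2) = -0.26, so the low-SEPR effect is overstated.

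**Effect of measurement error.** With reliability 0.80 per construct, the Case A coefficients at rho of -0.3 and -0.5 become -0.06 × 0.80 = -0.048 and -0.10 × 0.80 = -0.08. The false-positive rates fall to about 13% and 28%.

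**The case against.** The strongest objection is that everything depends on a correlation that the documents do not report. The passage on tonic activity dampening phasic activity describes upregulation under stress, not a correlation across children. Task 2.1 expects behavioral inhibition to rise with both BPS and SEPR, which does not sit easily with a strong negative correlation. This stands, and it makes the point conditional. It does not make separate models safe: they are unbiased for the adjusted effect only if rho is near zero or the other index has no effect on the outcome, and the protocol asserts neither.

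A reader might infer more than the text supports:

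- **That a BPS effect must appear as a low-SEPR effect.** The sign follows rho, and at -0.1 the distortion is small.
- **That a true SEPR effect on internalizing is masked.** It is attenuated, and only if rho is negative and BPS also raises internalizing. The introduction and the Task 3.2 expectations do link higher values of both indices to internalizing, so this case is within the protocol's own thinking.
- **That a large baseline pupil leaves less room to dilate.** The document does not say so. That SEPR is computed by subtracting the same trial's BPS is a natural reading, but it is not stated, and scoring detail may properly sit in a fuller plan.
- **That the whole study is affected.** Task 3.1 names BPS and SEPR together without saying whether they share a model, Task 3.2 is silent, and Work Package 4 uses tonic and phasic activity jointly.

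It can also be said that separate models match hypotheses worded as correlations. That stands for total associations. If tonic activity lowers phasic activity, SEPR lies downstream of BPS, and a joint model gives only the direct BPS path. The separate models should therefore be kept alongside the joint ones.

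**Conclusion.** The point holds in a conditional form for Task 2.2. The plan fixes separate models for two indices that it describes as linked, and it attaches to them hypotheses that need the two effects told apart. Across assumed correlations of -0.1 to -0.5, the consequence runs from negligible to material: a nominal 5% error rate of about 6% to 41% for an SEPR with no effect, and a true effect of 0.2 estimated at 0.18 to 0.10 when BPS also acts on internalizing. These figures rest on a BPS effect of 0.2, 300 children and error-free measures; lower reliability shrinks them. The documents settle neither the sign nor the size of the correlation, so they do not show that the planned results will be wrong in a particular direction. They do show that separate models alone cannot support a tonic-versus-phasic conclusion in Task 2.2.

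**What to change.** In Task 2.2, add models with BPS and SEPR as correlated predictors or mediators, and state that tonic-versus-phasic conclusions rest on the mutually adjusted paths. Keep the separate models and label them as total (marginal) associations. Report the BPS-SEPR correlation from the validation phase, which measures both indices before the longitudinal analyses. State that Tasks 3.1 and 3.2 use the same joint specification.

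No new data are needed, since both indices are assessed on every trial. The statistical cost is a variance inflation of 1/(1 − rho²): 1/(1 − 0.09) = 1.10 at |rho| of 0.3 and 1/(1 − 0.25) = 1.33 at 0.5. The interpretive cost is that the adjusted BPS path is a direct rather than a total effect and should be reported as such.

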#### Expected Outcome and Study Hypotheses

We hypothesize associations between retrospective childhood adversity, LC-NE function, and transdiagnostic psychopathology. For example, lower LC-NE tonic activity is expected to represent a resilience to the negative impact of childhood adversity on psychopathology. In addition, we expect profiles of LC-NE functioning that are associated with patterns of transdiagnostic psychopathology; BPS is expected to positively correlate with the p-factor, whereas increased and decreased SEPR are expected to positively correlate with internalizing and externalizing symptoms, respectively.

#### Risk Assessment, Participant Burden, and Ethical Considerations

We anticipate that some children will require immediate support, and we will use our clinical infrastructure to provide further case management. In addition, reports of adversity will be evaluated according to our in-house reporting guidelines, which align with the German child protection laws. This includes evaluation in a joint discussion and may result in reporting to child protection authorities when imminent danger is identified.

### Work Package 3 (Objective 3): Prospective Effect of LC-NE Functioning in a Developmental Model of Vulnerability and Stress

#### Task 3.1: LC-NE Functioning Predicts Later Transdiagnostic Psychopathology.

##### Participants

The study will follow the sample of 300 preschool-aged children, initially assessed in Task 2.2 at 4‐6 years of age across 3 time points.

##### Sample Size and Power

For the core longitudinal study with a cross-lagged panel model, power is *β*=.82 for 300 participants to detect a moderate cross-lagged effect of LC-NE functioning on psychopathology (a=0.2; see Figure 6).

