##### Risk Assessment

A major risk is a low retention rate. A meta-analysis identified a mean retention rate of 73.5% and identified strategies to increase it [102]. This includes barrier reduction by including remote data collection (eg, offer data collection via phone and online), tracing strategies by locator documents with contact information, and community-building by sending participants thank-you, birthday, and holiday cards. We will implement these strategies in LOCUS-MENTAL to maximize our retention rate while maintaining ethical standards.

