### Limitations

The novelty of the paradigms for preschoolers is a limitation since established pupillometric paradigms for assessing specifically LC-NE functions have not been established in young children. The dedicated validation phase (working package 1) is specifically designed to address this issue. Another limiting factor is the longitudinal study design. This design comes with the risk of high participants’ attrition, which may affect the final statistical power. To address this, the study will use retention strategies (eg, regular contact, family-friendly appointment scheduling, and compensation) and will use appropriate statistical methods to handle missing data.

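### Task 3.1 states power of .82 for the same 300 children it enrols, with no visible allowance for loss; at the cited 73.5% retention that figure scales to about .69 to .76

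*Protocol article*

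**What the plan says.** All places are in the protocol article.

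- **Task 3.1, Sample Size and Power:** power is .82, written, from after the decimal point, as "82 for 300 participants to detect a moderate cross-lagged effect of LC-NE functioning on psychopathology (a=0.2; see Figure 6".
- **Task 3.1, Participants:** "The study will follow the sample of 300 preschool-aged children, initially assessed in Task 2.2". The number enrolled at T1 and the number in the power statement are therefore the same.
- **Task 3.1, Risk Assessment:** low retention is called a major risk. "A meta-analysis identified a mean retention rate of 73.5% and identified strategies to increase it". Remote data collection, tracing and community-building are adopted in response. This is the only retention figure given for the longitudinal part.
- **Sample Size and Power (general section of Methods):** sample sizes rest on recruitment feasibility and on power above .80 for moderate effects. Power was estimated by Monte Carlo simulation with 1000 runs. No attrition setting is mentioned.
- **Limitations:** attrition is named as a risk "which may affect the final statistical power", without a figure.
- **Missing-data paragraph under Ethical Considerations:** mixed models and structural equation models are to handle missing waves, with pattern-mixture models and inverse probability weighting for non-random dropout.

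**The concern.** A cross-lagged path from pupillometry to later psychopathology is estimated from children who have the later CBCL. A child who leaves before that wave adds essentially no information on that path, whatever missing-data method is used. If .82 was computed with 300 children at every wave, it describes a study without dropout, while the same task warns of substantial dropout.

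This is the analysis behind the primary aim. The margin over the .80 target is only .02, so modest loss removes it. A null result would then be read against a miss rate of 18% (1 − .82), when a rate of 24% to 31% (1 − .76 to 1 − .69) may be nearer the truth.

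**Working it through.** **Inputs from the article:** power .82, n = 300, a = 0.2, target above .80, cited retention 73.5%, three annual waves.

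**Assumptions, because the article does not state them:** two-sided alpha of 5%; 73.5% is overall retention to T3; loss is even over the two years; dropout is at random.

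**1. Can .82 be reproduced?** Not exactly. Alpha, autoregressive paths, error variances and any equality constraints are not in the text, and Figure 6 is not shown. Trials at n = 300 and a = 0.2 gave:
- simple correlation of 0.2 (Fisher z): .94 at two-sided 5%;
- single-lag regression without measurement error: about .87 to above .99, for autoregression 0 to .7 and T1 correlation 0 to .5;
- simulated three-wave panel with assumed reliability .7, autoregression .5 and T1 correlation .2: .84 to .85 for each lag taken alone.

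So .82 is plausible. It is neither verified nor shown to be wrong, and the rest takes it as given.

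**2. Scaling.** The noncentrality implied by .82 is 1.960 + 0.915 = 2.875. If a fraction f of the information is retained, power = Φ(2.875·√f − 1.960). Apart from alpha, this needs none of the unstated model inputs.

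Even yearly loss to 73.5% gives √.735 = .857 at T2, so 300 × .857 = 257 children, and 300 × .735 = 220 at T3.

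| Path to which .82 is taken to refer | f | Power |
|---|---|---|
| T1 to T2 (257 children) | .857 | .76 |
| Path that needs T3 data (220 children) | .735 | .69 |
| One path shared over both lags, even loss | (.857 + .735)/2 = .796 | .73 |
| One path shared, all loss after T2 | (1 + .735)/2 = .867 | .76 |

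For example, at T3: 2.875 × .857 − 1.960 = 0.50, and Φ(0.50) = .69. With a one-sided 5% test the T3 figure is .71.

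**3. Size against simulation error.** With 1000 runs, the standard error of .82 is √(.82 × .18/1000) = .012. The drop of .06 to .13 is well beyond that.

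**4. Cross-check.** In the assumed panel simulation with reliability .7, retention of 85.7% and 73.5% took power from .85 to .78 (T1 to T2) and from .84 to .70 (T2 to T3). The direction and size agree with the scaling.

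**5. Retention needed for .80.** f = ((1.960 + 0.842)/2.875)² = .949 before rounding of the inputs, or about 285 of 300 children contributing to the path. At f = .90, power is .78. Under even loss, f = .949 corresponds to T3 retention of about 95% for a path that needs T3 data. For a shared path it is about 93%: (s + s²)/2 = .949 gives s = .966 and s² = .933. For a T1-to-T2 path it is about 90% (.949²).

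**6. Effect detectable with .82 at 220 children.** 0.2/√.735 = 0.233.

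**7. Sensitivity to the reading of 73.5%.** Read as retention per wave, it leaves 300 × .735² = 162 at T3. Power is then .56 for a path that needs T3 data and .63 for a shared path.

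**The case against.** The strongest reply is that 73.5% is not this study's planned retention. It is the mean from a cited meta-analysis, given as the reason for strategies meant to do better. That stands: a reader might infer that the plan expects to lose 26.5% of its cohort, and the article does not say so. The point survives because it does not depend on that figure. At 90% retained information, power is already below .80.

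Second, a reader might infer that .82 is an arithmetic error, or that the sponsor's own calculation yields .69 to .76. Neither is supported. The simulation cannot be rerun from the article, and the figures here rescale its result. That attrition was left out is inferred from the enrolled and powered numbers being equal. It is not stated, and simulation settings may sit in a fuller document.

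Third, partial data and remote collection soften the loss. This stands in part. The .73 to .76 for a shared path already credits partial records. Obtaining the caregiver CBCL by phone or online could raise the T1-to-T2 figure, since its predictor is measured at enrolment. It cannot replace laboratory pupillometry at T2, so the T2-to-T3 path still loses its predictor. Pattern-mixture models and weighting address bias and do not restore power.

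Fourth, the risk is disclosed: the Limitations section says attrition may affect power. That is fair, but no size is attached, and the only number a reader sees is .82.

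Finally, a reader might take the general power section as claiming that every task exceeds .80. It makes no such claim. It gives that level as a sample-size target, and Task 2.2 openly reports .80.

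**Conclusion.** The point holds as one about a power figure that shows no allowance for loss to follow-up. At the cited benchmark, .82 becomes about .76 for a T1-to-T2 path, .69 for a path that needs T3 data, and .73 to .76 for a shared path. The .76 for T1 to T2 belongs to 257 children and must not be attached to the 220 at T3, where the figure is .69.

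These values rest on accepting .82 at n = 300, a two-sided 5% test, 73.5% as overall retention to T3, even yearly loss (except where all loss is placed after T2) and dropout at random. The conclusion that the .80 target is missed rests on less: it follows whenever fewer than about 285 of 300 children contribute to the path. It would fall away if the simulation already included realistic attrition, which the article does not say.

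**What to change.** Keep enrolment at 300. Rerun the existing simulation with the expected numbers at T2 and T3 over a range of retention, for example 73.5% to 95%, and state alpha and which path the power refers to. Restate Task 3.1 power accordingly. At 73.5%, expect about .69 to .76 for a = 0.2, or .82 for a of about 0.23 with 220 children. If the simulation already included attrition, one clause giving the assumed rate settles the matter.

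The cost is one rerun of existing code and one revised sentence, with a less favourable figure. Design and analysis do not change. The longitudinal phase is scheduled to start in April 2026, so the restatement is best made before follow-up data accrue.
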